**Figure 2 F2:**
[figure not shown]
**Exercise interventions and timeline**.

### Exercise Intervention (group 1)

The exercise program will be undertaken twice weekly in small groups of participants and will be supervised by the exercise physiologist over 6 months. This group will also have access to Internet resources where they will be able to input information regarding their weekly physical activity. Sessions will comprise aerobic and resistance exercise using a variety of equipment. In addition, 2 exercise sessions will be completed at home each week comprising aerobic exercise (e.g. walking). The clinic sessions, which will commence with a warm-up and finish with a cool-down (comprising exercise on a cycle ergometer or treadmill at a relatively low intensity and stretching activities), will take approximately 60 minutes and will be conducted in local exercise facilities. The moderate- to high-intensity progressive resistance training regime will include 7 exercises that target the major upper and lower body muscle groups, which we have used previously in a number of studies including those with prostate cancer patients [19,24-27]. The exercises are the chest press, seated row, shoulder press, leg press, leg extension, leg curl and abdominal crunches. The resistance exercise program is designed to progress from 12 to 6-repetition maximum (RM) for 2 to 4 sets per exercise. Each clinic session will include 20-30 minutes of aerobic exercise using various modes such as walking or jogging on a treadmill, cycling or rowing stationary ergometers. Target intensity will be 70-85% of estimated maximum heart rate with individual heart rate monitors provided for each participant. During the 6-month follow-up period, this group will have access to a booklet with detailed information about a home exercise prescription but will no longer receive exercise supervision. The home exercise program combines resistance training (using body weight, rubber bands, and objects around the house as a resistance and is designed to replicate the exercises performed in the supervised sessions), aerobic training, and flexibility exercises.

### Standard Physical Activity Recommendation (group 2)

The standard physical activity recommendation group (control condition) will be instructed via printed material to perform the general recommendation of 30 minutes of moderate/vigorous physical activity 5 days per week (150 minutes per week of moderate activity) during the initial 6-month period as well as the 6-month follow-up period. At the completion of the study, this group will be given access to the booklet with detailed information about a home exercise prescription and internet resources developed during the course of the study to encourage exercise adoption. Instruction on performing the home-based exercises will be provided by the exercise physiologist (this will take place at the end of the 6-month follow-up).

### Study Endpoints

Measurements will take place at baseline, 6 months (end of the supervised exercise intervention period), and at 6 months follow-up. The assessment at 6 months follow-up is to determine the long-term effects and whether differences observed directly following the intervention are maintained in the exercise group when the booklet of standard physical activity recommendations is supplemented with the home exercise prescription.

### Aerobic Walking Capacity

As a measure of quantitative aerobic walking endurance capacity, subjects will undertake a timed 400-m walk, 10 laps out and back over a 20-m corridor path [19,28,29].

### Anthropometric Measures/Abdominal Obesity

Central adiposity will be assessed by waist circumference (WC) and hip circumference (HC) will also be determined [30]. WC will be measured at the level of the narrowest point between the lower costal (rib) border and the iliac crest. HC will be measured at the level of the greatest posterior protuberance of the buttocks which usually corresponds anteriorly to the level of the symphysis pubis. The waist-to-hip ratio will be determined and has been shown to be a strong indicator of atherosclerosis and risk of myocardial infarction [31,32]. Body mass index (kg/m^2^) will also be used to assess weight (kg) relative to height (m) and is a good indicator of obesity and metabolic and health-related problems.

### Blood Markers

Testosterone, prostate specific antigen (PSA), insulin, lipid profile, glucose and HbA_1c _levels will be measured commercially by accredited Australian National Association of Testing Authorities (NATA) and International Accreditation New Zealand (IANZ) laboratories.

### Self-reported Physical Activity

Self-reported physical activity will be assessed by the leisure score index from the Godin Leisure-Time Exercise Questionnaire. Overall physical function will also be assessed qualitatively using the SF-36 physical function sub-scale. In addition, participants will wear a pedometer for seven days at the three measurements time points to obtain a quantitative measure of steps per day.

### Quality of Life, Falls Self-Efficacy and Psychological Distress

Health-related quality of life will be measured using the EORTC QLQ-C30 and EORTC QLQ-PR25 as well as a health history questionnaire [3,33]. This validated instrument is an integrated system to assess quality of life in cancer patients and has been extensively employed in clinical trials [34]. The Brief Symptom Inventory-18 (BSI-18) will be used to assess psychological distress (Anxiety, Depression and Somatisation) [35]. Falls self-efficacy was determined using the activities-specific balance (ABC) confidence scale [36].

### Nutrition

Participants will be encouraged to maintain customary activity and dietary patterns and the mini nutritional assessment (MNA) instrument will be used to monitor nutritional status [37].

### Lower Body Physical Function

Lower body performance will be assessed by the repeated chair rise test, where subjects rise to a standing position five times as fast as possible without using their hands for support [19,25].

### Additional Measures for the Perth Site

In addition to the above measures, participants at the Perth site will have the following assessments undertaken at the same 3 time points.

### Body Composition

Whole body lean mass (LM), fat mass (FM), and percent fat will be assessed by dual-energy X-ray absorptiometry (DXA, Hologic Discovery A, Waltham, MA). From the whole body scan, upper limb, lower limb, and trunk LM and FM will be derived by manipulating segmental lines according to anatomical landmarks [38]. Upper limb LM and lower limb LM will then summed to derive appendicular skeletal muscle [39].

### Muscle Strength

Dynamic concentric muscle strength will be measured using the one repetition maximum (1-RM) method. The 1-RM is the maximal weight an individual can move through a full range of motion without change in body position other than that dictated by the specific exercise motion [25].

### Balance and Risk of Falling

A Neurocom Smart Balancemaster (Neurocom, OR, USA) will be used to assess static and dynamic balance. This device measures ground reaction force to track whole body centre of pressure and a tilting visual field and support platform to separate the visual, somatosensory and vestibular balance sense of the patient. As a measure of dynamic balance, subjects will also walk backwards 6-m and time taken will be assessed using electronic timing gates [25].

### Calculation of Sample Size and Statistical Analysis

The sample size estimate was based on projected changes in aerobic walking capacity (cardiorespiratory fitness) as measured by the 400-m walk as this study endpoint has been shown to be a strong predictor of mortality, CVD and mobility limitations in older adults [28,40,41]. To achieve 80% power at α = 0.05 (two-tailed), 142 subjects per group are required to demonstrate a 0.33 SD difference between groups at the end of the 6-month intervention and follow-up periods. Previous experience with exercise trials indicates an attrition rate of up to 30% over the course of the study period. Therefore, to ensure that we have sufficient subject numbers at the end of the intervention and follow-up periods, 185 subjects will be randomized to each of the groups (N = 370). Regarding the other outcomes, a sample size of 370 will account for expected differences. Data will be analysed using the SPSS statistical software package. Analyses will include standard descriptive statistics, Student's t tests, correlation and regression, and two-way (group × time) repeated measures ANOVA to examine differences between groups over time. All tests will be two-tailed and an alpha level of 0.05 will be applied as the criterion for statistical significance.

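### The 30% attrition allowance is too small: 185 per group leaves about 129 at that rate, not the 142 the protocol requires for 80% power

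*Protocol article*

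**What the plan says.** All the relevant figures stand in one paragraph of the protocol article, under Calculation of Sample Size and Statistical Analysis.

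- **Requirement.** At 80% power and two-sided α of 0.05, "142 subjects per group are required to demonstrate a 0.33 SD difference between groups at the end of the 6-month intervention and follow-up periods".
- **Endpoint.** The sizing rests on "projected changes in aerobic walking capacity (cardiorespiratory fitness) as measured by the 400-m walk".
- **Planned loss.** "Previous experience with exercise trials indicates an attrition rate of up to 30% over the course of the study period".
- **Conclusion drawn.** So that enough men remain at both time points, "185 subjects will be randomized to each of the groups (N = 370").

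No inflation formula is printed and no other reason for 185 is given. For the remaining outcomes the section says only that 370 will be adequate, so this is the only power calculation in the document.

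**The concern.** The number randomised is presented as following from the requirement and the attrition rate. If 30% of 185 are lost, fewer than 142 remain, so it does not follow. The likely cause is a common slip: adding 30% to the required number instead of dividing by the proportion expected to remain. The two routes differ because the 30% loss applies to everyone randomised, not to the 142 who must complete.

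At stake is the design's headline claim. If attrition comes near the planned ceiling, a null result on the 400-m walk would be judged against 80% power when the chance of missing the target effect was about 25%, not 20%. This bears most on the follow-up assessment, where cumulative attrition is greatest and where the trial asks whether gains are maintained.

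**Working it through.** **Inputs**, all from the sample-size section except the 1:1 allocation (Randomization and Stratification): two-sided α 0.05; power 80%; difference 0.33 SD; 142 required per group; attrition up to 30%; 185 randomised per group.

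**1. Reproduce the 142.** The normal approximation is n per group = 2(z₀.₉₇₅ + z₀.₈₀)² / δ², with z values 1.960 and 0.842.
- δ = 0.33: 2 × 7.849 / 0.1089 = 144.2, so 145 (t-based 145.1).
- δ = 1/3: 2 × 7.849 × 9 = 141.3, so 142 (t-based 142.2).

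The stated 142 is therefore the answer for an unadjusted two-group comparison at 1/3 SD, printed as 0.33. That rounding is not an error worth raising.

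**2. Reproduce the 185.**
- Multiplying: 142 × (1 + 0.30) = 184.6, so 185. This is the printed figure.
- Dividing: 142 / (1 − 0.30) = 202.9, so 203 per group, 406 in total. This does not match.

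That the multiplication was used is an inference, but the shortfall in step 3 does not depend on it.

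**3. Numbers remaining at 30% attrition.** 185 × 0.70 = 129.5, so 129 or 130 per group against 142 required.

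**4. Power of the two-sample t-test, two-sided 0.05.**

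| n per group | 0.33 SD | 1/3 SD |
|---|---|---|
| 142 (as required) | 79.1% | 79.9% |
| 130 | 75.5% | 76.3% |
| 129 | 75.2% | 76.0% |

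At a fixed effect size, going from 142 to 129 costs about 3.9 points.

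**5. Difference detectable with 80% power at 129 per group.** 2.802 × √(2/129) = 0.349 SD (t-based 0.350 SD).

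**6. Attrition that 185 per group can absorb.** 1 − 142/185 = 23.2%. If 146 per group are taken as needed at exactly 0.33 SD, it is 1 − 146/185 = 21.1%.

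**7. Power for 0.33 SD across attrition rates, starting from 185 per group.**

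| Attrition | Remaining per group | Power |
|---|---|---|
| 10% | 166.5 | 85.1% |
| 15% | 157.3 | 83.1% |
| 20% | 148.0 | 80.8% |
| 25% | 138.8 | 78.2% |
| 30% | 129.5 | 75.3% |

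**8. What baseline adjustment could recover.** With analysis of covariance, the required n is approximately 145.1 × (1 − r²), where r is the correlation between baseline and outcome: 132 at r = 0.3, 122 at r = 0.4, 109 at r = 0.5. Setting this equal to 129 gives r² = 1 − 129/145.1 = 0.111, so r is about 0.33. The protocol states no r, so these values are assumptions. The gain also requires that the 0.33 SD refers to the SD of the outcome itself.

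**The case against.** Four points can be made for the protocol.

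- **The 30% is a ceiling for the whole study.** Up to 23.2% attrition, 185 per group still leaves 142. Losses by the end of the 6-month intervention cannot exceed the whole-study figure and are probably lower; at an assumed 20% power would be 80.8%. This stands: the deficit is shown only for attrition above about 23%, and chiefly at follow-up. But the paragraph uses the ceiling to justify 185, names no lower expected rate, and promises adequate numbers at both time points.
- **The loss is smaller than 80% against 75% suggests.** Also true. Even 142 per group gives only 79.1% at exactly 0.33 SD, so the attrition step itself costs about 4 points, and the detectable difference rises by less than 0.02 SD.
- **The planned analyses may be more efficient than a t-test.** The section also lists regression and repeated measures ANOVA, and a modest baseline correlation would restore 80%. This softens the consequence. It does not rescue the stated figure, because 142 is the unadjusted number and the calculation claims no gain from adjustment.
- **The multiplication by 1.3 is inferred.** True, but 70% of 185 is below 142 by any route.

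**Conclusion.** The concern holds. The protocol's own figures conflict: at the attrition it plans for, 185 per group leaves 129 to 130 men, not 142. Power for 0.33 SD is then about 75% (76% at 1/3 SD), and 80% power is reached only for about 0.35 SD. These figures assume equal attrition in the two groups, an unadjusted two-sided comparison at 0.05, and attrition at the stated ceiling. The stated power is sound if attrition stays at or below about 23%. The treatment estimate and type I error are unaffected. The effect is modest, but the statement is wrong as written and should be corrected, because it is the only power claim in the document.

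**What to change.** Keep N = 370 and correct the sentence, for example:

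> With 30% attrition about 129 men per group remain, giving about 75% power for a difference of 0.33 SD, or 80% power for 0.35 SD, by an unadjusted comparison. The 142 per group are retained only if attrition is no more than 23%.

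Alternatively, base the calculation on a baseline-adjusted analysis. State the assumed correlation of baseline with the 6-month value and with the follow-up value, give its justification, and make clear which SD the 0.33 refers to. A correlation of about 0.33 or more restores 80% power with 129 per group.

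Keeping both the unadjusted calculation and the full 30% allowance would take 203 per group (406 in total, 36 more men), but that is not needed to make the text correct. The recommended change costs one sentence and a slightly less favourable power statement. It needs no extra patients and no change in conduct.

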The purpose of this study is to determine the effects, efficacy, retention and compliance of a physical exercise intervention in a large established cohort of prostate cancer patients from the RADAR study. Specifically, we aim to compare short- and long-term effects of a prostate cancer-specific supervised exercise program to educational material of physical activity utilizing printed resources on cardiovascular and metabolic risk factors. Our primary outcomes are cardiorespiratory capacity, abdominal obesity, and lipid and glycemic control, while secondary outcomes include self-reported physical activity, quality of life and psychological distress. Our hypothesis is that compared to a standard physical activity recommendation (e.g. perform 30 minutes of moderate/vigorous physical activity 5 days of the week), the prostate cancer-specific supervised exercise intervention will elicit superior adaptations in: improving physical/cardiorespiratory capacity; body composition (reducing abdominal fat mass); glycemic control and lipid metabolism; enhancing self-reported physical activity, quality of life and psychological distress. This project has the potential to elicit positive health benefits for large numbers of men with prostate cancer. It is a lifestyle intervention that allows patients some control and personal responsibility and, as such, could easily be expanded to all such patients resulting in a considerable reduction in morbidity and mortality.

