### Randomization and Stratification

Patients will be randomly allocated to the two treatment arms: (1) exercise and (2) standard physical activity recommendation in a ratio of 1:1, subject to maintaining approximate balance regarding stratification for age (<69, 69-74, >74), original RADAR study arm [(A) 6-month ADT and radiation; (B) 6-month ADT, radiation and 18-month bisphosphonate; (C) 18-month ADT and radiation; and (D) 18-month ADT, radiation and 18-month bisphosphonate], current levels of testosterone (<3, 3-8, >8), and waist circumference (< or > than 102 cm) (Figure 2).

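### The statement that 370 men suffice for the other outcomes cannot apply to the measures taken only at Perth, and is unsupported there

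*Protocol article*

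**What the plan says.** Under Calculation of Sample Size and Statistical Analysis, one endpoint drives the size: "The sample size estimate was based on projected changes in aerobic walking capacity (cardiorespiratory fitness) as measured by the 400-m walk". The calculation reads: "To achieve 80% power at α = 0.05 (two-tailed), 142 subjects per group are required to demonstrate a 0.33 SD difference between groups". Past experience "indicates an attrition rate of up to 30% over the course of the study period", and 185 men per group (370 in total) are to be randomized. The section then turns to everything else in a single sentence: "Regarding the other outcomes, a sample size of 370 will account for expected differences". It gives no expected difference, SD or number for any of these outcomes.

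The Abstract states that the 370 come from Perth, Newcastle and Wellington together. Under Additional Measures for the Perth Site, "participants at the Perth site will have the following assessments undertaken at the same 3 time points". The sections that follow list DXA lean and fat mass (whole body, limbs and trunk), 1-RM strength, Neurocom balance and a timed 6-m backward walk.

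The hypothesis in the Background includes better body composition, specified as less abdominal fat mass. Under Anthropometric Measures/Abdominal Obesity, central adiposity is assessed by waist circumference, with hip circumference, waist-to-hip ratio and BMI, and this is not restricted to one site.

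**The concern.** The adequacy sentence rests on 370 men and carries no qualification. A measure taken at one of three sites cannot be taken in all 370, so for the Perth measures the sentence refers to a sample that the design does not provide.

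Two of these measures bear on what the article sets out to show. DXA is the only measure of fat mass in the document, and fat mass is the term used in the hypothesis. 1-RM is the only direct strength test, and the Discussion promises information on muscle function. A reader told that 370 is enough for the other outcomes could take a null DXA, strength or balance result as evidence of no effect, when the subset might have had little chance of detecting a moderate one.

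**Working it through.** **Inputs from the protocol article.** Two-sided alpha 0.05; 80% power; 0.33 SD and 142 per group (for the 400-m walk); 185 randomized per group; allocation "in a ratio of 1:1"; attrition up to 30%; three sites.

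**Assumptions.** The Perth share *s* of the 370 is not stated, so a range is used. Perth men are taken to split equally between the groups; site is not among the listed stratification factors, so this is approximate. The comparison is unadjusted.

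**1. The article's own figure.** n per group = 2(1.960 + 0.842)² / d².
- d = 0.33: 144.1, rounded up to 145.
- d = 1/3: 141.3, rounded up to 142.

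So 142 is reproduced with 0.33 read as one third. The 185 is 142 × 1.3 = 184.6.

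**2. Outcomes measured at all sites.** Completers per group at 30% loss: 185 × 0.7 = 129.5. The difference detectable with 80% power is 2.802 × √(2/129.5) = 0.348, about 0.35 SD. Power at 0.33 SD is 75.7%. With no loss, 185 per group gives 0.29 SD.

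**3. Perth-only measures.** Per group: 185 × *s* without loss and 185 × *s* × 0.7 with 30% loss. Detectable difference = 2.802 × √(2/n). For example, with *s* = 25%: 185 × 0.25 × 0.7 = 32.4, and 2.802 × √(2/32.4) = 0.70 SD.

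| Assumed Perth share | Men at Perth | Per group, no loss / 30% loss | Detectable at 80% power (SD), no loss / 30% loss | Power at 0.33 SD, no loss / 30% loss |
|---|---|---|---|---|
| 25% | 92 | 46.2 / 32.4 | 0.58 / 0.70 | 36% / 26% |
| one third | 123 | 61.7 / 43.2 | 0.50 / 0.60 | 45% / 34% |
| 50% | 185 | 92.5 / 64.8 | 0.41 / 0.49 | 61% / 47% |
| two thirds | 247 | 123.3 / 86.3 | 0.36 / 0.43 | 74% / 58% |
| 90% | 333 | 166.5 / 116.5 | 0.31 / 0.37 | 85% / 71% |

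The last column uses 0.33 SD only as a common yardstick; the article states that figure for the 400-m walk alone. Figures are from the normal formula; a t-based calculation differs by about 0.01 SD or one percentage point.

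**4. Two bounds that need no assumed share.**
- At 30% loss, even all 370 men give 75.7% power at 0.33 SD, so any Perth subset has less.
- With no loss at all, Perth would need 145/185 = 78% of all the men to reach 80% power at 0.33 SD.

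**The case against.** The strongest reply is that the sentence was never meant to cover Perth. The Abstract and Background list the outcomes: cardiorespiratory capacity, abdominal obesity, and lipid and glycemic control as primary; self-reported activity, quality of life and distress as secondary. Each has a measure at every site. The Perth tests sit apart under a heading that calls them additional. On that reading 370 is the right total. It is a fair reading, but the sentence does not say so, and the secondary list is introduced as inclusive rather than complete. The ambiguity can be removed with a few words.

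A second reply is that per-outcome power and site-level numbers are commonly left out of an article. That stands: their absence is not the point. The point is an affirmative claim of adequacy that the design does not deliver for some of the measures described.

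Two stronger readings are tempting, and the documents do not support them.
- A reader might infer that the claim is false for Perth, or that the Perth comparisons are underpowered. The Perth number and the expected effects are not given. An effect of about 0.5 to 0.7 SD could be detectable with a share of 25% to 50%.
- A reader might infer that the abdominal part of the hypothesis cannot be tested in the full sample. Waist circumference tests it at all sites. Moreover, DXA as described yields trunk fat, not a defined abdominal region, so it is a direct measure of fat mass but not of abdominal fat specifically.

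**Conclusion.** The adequacy statement is inapplicable to the Perth-only measures and unsupported for them. This follows from the text alone, whatever Perth's share. How far those measures fall short is not determined by the document. Under assumed shares of 25%, one third and 50% with 30% attrition, the difference detectable with 80% power is about 0.70, 0.60 and 0.49 SD, compared with about 0.35 SD for outcomes measured at all sites. No primary comparison depends on Perth. The sentence should be corrected because it states a size that part of the design does not have, but the correction is one of scope and labelling and leaves the design as it is.

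**What to change.** Replace the adequacy sentence with wording such as:

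> With about 129 completers per group (185 less 30%), outcomes measured at all three sites have 80% power for a difference of about 0.35 SD (two-sided alpha 0.05, unadjusted). DXA body composition, 1-RM strength, Neurocom balance and the backward walk are measured at Perth only and are exploratory; with [expected completers per group at Perth] the difference detectable with 80% power is [x] SD.

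The sponsor supplies the expected Perth number, and x follows as 2.802 × √(2/n). In the hypothesis, name waist circumference as the measure for the abdominal component, with DXA fat mass as supportive evidence from Perth.

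The cost is wording only: recruitment, assessments and patient burden do not change. The downside is a less favourable stated adequacy for the Perth measures.

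### The three-visit group × time repeated-measures ANOVA is not the contrast the trial was sized on, discards observed data from men with a missing visit, and cannot show whether an effect is maintained

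*Protocol article*

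**What the plan says.** All of the analysis text is in the Protocol article, under Calculation of Sample Size and Statistical Analysis. The sample size sentence targets "a 0.33 SD difference between groups at the end of the 6-month intervention and follow-up periods", and concludes that "142 subjects per group are required" for 80% power at a two-sided 5% level. The same paragraph expects "an attrition rate of up to 30% over the course of the study period" and raises the number randomised to 185 per group, 370 in all.

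The methods are then listed: descriptive statistics, Student's t tests, correlation and regression, and a "two-way (group × time) repeated measures ANOVA to examine differences between groups over time", all in SPSS. The ANOVA is the only method given a stated purpose. No method is named as the deciding one.

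The visit schedule is under Study Endpoints: "Measurements will take place at baseline, 6 months (end of the supervised exercise intervention period), and at 6 months follow-up". That section explains that the last visit is there to see whether differences present after the intervention persist. The Discussion lists the maintenance of gains as one of two specific aims.

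**The concern.** Three features of the named method fit badly with the rest of the paragraph.

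- **Complete data.** A classical repeated-measures ANOVA needs a value at every visit. A man who attends at 6 months but not at 12 months drops out of the whole analysis, including the 6-month comparison to which he contributed. A trial that expects substantial attrition has reason to avoid this.
- **Target.** The group × time term over three visits is a 2-df test of any departure from parallel profiles. The sample size is for a difference between two groups at a time point.
- **Interpretation.** A significant interaction does not say at which visit the groups differ, or in which direction. The trial wants to know whether a 6-month gain is kept at 12 months, and the omnibus test does not separate a kept gain from a lost one.

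At stake are observed 6-month data, possibly power, and a clear answer to the maintenance question.

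**Working it through.** **Inputs from the article.** Two-sided α = 0.05, power 80%, difference 0.33 SD, 142 evaluable and 185 randomised per group, attrition up to 30%, three visits.

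**Inputs assumed.** The article gives no correlation ρ between visits, so I use 0.3 to 0.8 with compound symmetry. It does not say whether the SD is of the outcome or of change; I take the outcome SD, set to 1.

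**1. The plan's own figure.** For two means, n = 2(1.960 + 0.842)²/d².
- d = 0.33: n = 144.1, rounded up to 145.
- d = 1/3: n = 141.3, rounded up to 142.

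The stated 142 is therefore a two-group, single-contrast calculation with no repeated-measures term.

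**2. Men with complete data.** At the full 30%, 185 × 0.70 = 129.5 per group, about 259 of 370. I use 129 per group below. This is under 142 because 185 is 142 × 1.3, whereas 142/0.70 = 203.

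**3. Degrees of freedom.** (2 − 1)(3 − 1) = 2 for group × time.

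**4. Power of the interaction test.** Let d be the group difference at each visit. The noncentrality is λ = (n/2) Σ(d − d̄)²/(1 − ρ), with 2 and 2(2n − 2) df.
- Sustained (0, 0.33, 0.33): Σ(d − d̄)² = 0.0726.
- Vanished by 12 months (0, 0.33, 0): Σ(d − d̄)² = 0.0726.
- Halved by 12 months (0, 0.33, 0.165): Σ(d − d̄)² = 0.05445.

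The sustained and vanished profiles give the same λ, hence the same power at every ρ. At ρ = 0.5, λ = 64.5 × 0.0726/0.5 = 9.37 and power is 78.5% for both.

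**5. Power of a single-visit contrast** (normal approximation). Adjusted for baseline, the residual SD is √(1 − ρ²), and power is Φ(0.33/[√(1 − ρ²) √(2/129)] − 1.96). Unadjusted, it is Φ(2.65 − 1.96), about 75% at any ρ.

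| ρ | F test, sustained | F test, halved | Baseline-adjusted contrast, 0.33 SD | Unadjusted t test |
|---|---|---|---|---|
| 0.3 | 63% | 50% | 79% | 75% |
| 0.5 | 79% | 65% | 86% | 75% |
| 0.6 | 87% | 76% | 91% | 75% |
| 0.7 | 95% | 87% | 96% | 75% |
| 0.8 | 99% | 97% | 99% | 75% |

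Against the baseline-adjusted contrast, the F test loses about 16, 8 and 1 points at ρ = 0.3, 0.5 and 0.7 if the effect is sustained, and 29, 21 and 9 points if it halves. For a sustained effect at ρ = 0.8 there is no loss.

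Every column uses the same 129 men per group, so these gaps do not measure the cost of deleting men. That cost comes on top, and depends on how many are seen at 6 months and missing at 12. As an illustration only, if 15% rather than 30% were missing at 6 months (about 157 per group), the baseline-adjusted 6-month contrast would have 87%, 92% and 98% at ρ = 0.3, 0.5 and 0.7.

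**The case against.** The case against has several parts, and much of it stands.

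- **Deletion is not written down.** The article is silent on missing data, and a fuller protocol or analysis plan may deal with it. That silence is no fault. The point rests only on what the named procedure does in its classical form.
- **The ANOVA is not declared the deciding test.** The listed t tests could test the powered contrast, and the listed regression could adjust for baseline. This stands. But the ANOVA is the only method tied to group differences over time, and nothing says the t tests decide.
- **A reader might infer that the ANOVA throws away 30% of the men, about 111 of 370.** The article does not support this. The 30% is an upper bound on attrition, which the sample size anticipates, and no model recovers outcomes that were never observed. What the ANOVA adds is the loss of men with some but not all follow-up visits, a share somewhere between 0 and 30%.
- **A reader might infer that power is always lost.** It is not. For a sustained effect, which is how the design sentence reads, the F test matches or beats the unadjusted t test (75%) at ρ of 0.5 or more. It is weaker at ρ = 0.3. Quoting only 65% against 86% would rely on a halved effect, ρ = 0.5 and a baseline-adjusted comparator.
- **A reader might infer a bias in favour of exercise.** If men in the exercise arm who responded poorly left after month 6, a completers' analysis could be biased that way. Nothing in the article establishes that mechanism or its size, so I put no figure on it.
- **A reader might want 12 months made secondary.** The sample size sentence covers the end of both periods, so the article gives no basis for that ranking.

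**Conclusion.** The point holds as a cheap improvement to a named method. It does not show that the trial's analysis is invalid.

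Three things are firm. The 142 per group comes from a single two-group contrast. The three-visit interaction is a 2-df test, which is a different thing. In its classical form it excludes men with any missing visit, together with the data they gave. Under compound symmetry it also has identical power for a maintained and a lost 12-month effect, so on its own it cannot answer the maintenance question. That last result needs no assumption about missing data or the value of ρ.

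The size of any power loss is conditional. Against a baseline-adjusted contrast it runs from none (ρ = 0.8, sustained) to about 29 points (ρ = 0.3, halved), with 129 completers per group. Neither ρ nor the effect profile is given. The number of observed 6-month results that would be lost cannot be computed from the article.

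**What to change.** Replace the repeated-measures ANOVA with wording such as:

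*The 6- and 12-month values will be analysed in a linear mixed model with baseline value, visit, group and group × visit, and an unstructured covariance. Every randomised man with at least one post-baseline value will be included, analysed as randomised. The group differences at 6 months and at 12 months will be estimated and reported separately.*

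Add one sentence saying which of the two contrasts decides the primary conclusion, or how the two are combined if both do. That choice is for the investigators.

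The MIXED procedure in SPSS fits this model, so software, data and visits stay the same. The cost is a little more analysis work and reliance on a missing-at-random assumption, which should be stated. Men with no post-baseline value are still not recovered.
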